### Ethics and data protection

The study was approved by the Ethics Committee of the Hannover Medical School in August 2018 (No.: 8038_BO_K_2018). Written informed consent will be obtained from all GPs, relatives of deceased patients and health care experts by the study team prior to any study procedure.

Each participant will be assigned with an individual code in order to pseudonymise the related data. The code list will be archived and locked separately from the data collection documents. Only study members will have full access to study material. Furthermore, GPs will list each deceased patient included for testing and assign them with an individual ID. That list remains in the general practices and will be inaccessible for the study team. Patient data collected and stated by the GPs in the questionnaires will be given anonymously to the research team so that patients’ identity will be fully preserved. Essential amendments to the study protocol or the interventions will be reported to the Ethics Committee of the Hannover Medical School for approval.

### Data analysis

Qualitative data: Interviews will be audio recorded, pseudonymised, transcribed, and analysed using the software MAXQDA. All transcripts will be analysed using qualitative content analysis as described by Mayring [38] and by Meuser and Nagel especially for the analysis of expert interviews [39].

Quantitative data: For data entry and data analyses the Statistical Package for the Social Sciences (SPSS) will be used. For the evaluation of the difference in the GP-EoLC-I between pre and post intervention phase paired t-test will be applied. To compare parameters of patients in the pre and in the post intervention phase different tests for independent samples will be performed depending of the underlying distribution of the outcome parameters (e.g. Mann-Whitney-U-test, χ^2^-test, and unpaired t-test). Secondary data analysis of claims data of the Local Health Care Fund (AOK) in Lower Saxony will be performed using descriptive analyses.

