### Phase I: exploration of usual practice (9 months)

In phase I, we explore the usual practice of care for patients with chronic progressive diseases in the last phase of life (baseline data collection, t_0_). Phase I comprises the following five work packages:Work package 1a: Guided expert interviews (*n* = 15) with health care stakeholders and PC providers of different settings focusing on infrastructure, collaboration, care experiences, and care situation.Work package 2a: Standardized written survey with GPs (*n* = 50) of 35 different single or group practices to give an insight into organization and quality of PC for patients in the last phase of life. For this purpose, we will use the German version of the General Practice End-of-Life Care Index (GP-EoLC-I) [31].Work package 3a: Guided after-death interviews with relatives (*n* = 25) of deceased patients of the 35 general practices focusing on how they experienced and perceived PC in the last phase of life in general and provided by GPs.Work package 4a: Analysis of clinical data of patients with chronic progressive diseases of the 35 collaborating general practices who died within a defined period of time. The analysis is based on key indicators (e.g. chemotherapy for cancer patients in the last month of life, number of hospitalisation and treatment days in the last six months of life, number of patients who died in the hospital) to evaluate the quality of care at the end of life [5].Work package 5a: Secondary data analysis of patients who died in a defined period of time before the intervention and were insured members of the Local Health Care Fund (AOK) in Lower Saxony. The analysis is based on key indicators to evaluate the quality of care at the end of life [5].

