
### Phase III: evaluation (15 months)

In phase III, process and outcome evaluation will give an insight into barriers, facilitating factors, effects of the intervention, and reveal information on possibilities for sustainable maintenance.Work package 8: This work package is part of the process evaluation. Protocols from the monitoring visits and reflection talks in the 35 general practices during the intervention (phase II) will be analysed. Results will give further information about the implementation process of the SPICT-DE in general practice and its practicability as well as efficacy in daily GPs’ practice.Work package 9: This work package is part of the outcome evaluation. GPs will be asked to fill out a single-page semi-structured questionnaire with six questions concerning alterations in the patients’ situation and the occurrence of any critical incidences for every patient after the first application of the SPICT-DE. A critical incidence is defined as e.g. acute crises in the disease progression, unplanned hospital admissions, changes in therapy, care, and living environment as well as death of patients. Furthermore, GPs will be asked to indicate for each patient if and if so which PC actions as recommended by the SPICT-DE were initiated. Analysis of the indicators of the SPICT-DE and of initiated PC actions will give further information on the effects of the intervention and the handling of SPICT-DE in daily practice.Work packages 1b-5b (follow-up, t_1_): These work packages will be performed in an equivalent way as described for the work packages 1a-5a of phase I (baseline data collection, t_0_): guided expert interviews (*n* = 15), standardized written survey with GPs (*n* = 50) of the 35 general practices, guided after-death interviews with relatives (*n* = 25) of deceased patients of the 35 general practices, analysis of clinical data of patients with chronic progressive diseases of the 35 collaborating general practices who died within a defined period of time, and secondary data analysis of patients who died in a defined period of time after the intervention and were insured members of the Local Health Care Fund (AOK) in Lower Saxony. Results of these work packages will allow the pre-post comparison.

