### Study population and recruitment

OPAL is addressed to four different target groups: (1) health care stakeholders, (2) GPs and their practice teams, (3) relatives of deceased patients with chronic progressive diseases, and (4) deceased patients with chronic progressive diseases.Health care stakeholders (*n* = 15) at the interfaces of PC and GP care such as e.g. nursing services, hospitals, hospices, and medical specialist PC teams will be informed about the project and invited by letter/mail and by telephone to take part in OPAL.GPs (*n* = 50) of 35 different general practices being registered in Hameln-Pyrmont will be informed about the project and invited by letter/mail and by telephone to take part in OPAL. GPs and their practice teams will receive an allowance for their participation in the study.Relatives (*n* = 25) of deceased patients of the 35 general practices are eligible when they meet the following inclusion criteria: age ≥ 18 years and a direct contact to the deceased patient in the last phase of their life (independent of sex and gender). Recruitment follows the principle of purposive sampling. The relatives are recruited by the GPs and their practice teams. To assure data protection, relatives will contact the study team when interested or their contact data will only be given to the study team by GPs and their practice teams after prior informed consent and permission. This procedure has been applied successfully in other studies [33–35].Patients (age ≥ 18 years, independent of sex and gender) with oncological and/or non-oncological chronic progressive diseases who died during a defined period of time before (t_0_) and after (t_1_) the intervention while being treated by one of the collaborating GPs will be included for further data analysis using standardized questionnaires. Furthermore, members (age ≥ 18 years, independent of collaborating GP practices as well as sex and gender) of the Local Health Care Fund AOK in Lower Saxony who died in a defined period of time before (t_0_) and after (t_1_) the intervention will be included in the secondary data analysis based on key indicators to evaluate the quality of care at the end of life [5]. An exclusion criterion for both groups of deceased patients is sudden death, which cannot be related to a chronic progressive disease (e.g. traffic accident, heart attack without prior diagnosis of coronary heart disease).

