### Sample size calculation

Main target of the intervention are GPs in Hameln-Pyrmont (work package 2a and 2b). A total of 105 GPs is registered in 75 general practices in this region. Based on the recruitment rates of previous studies a participation of 50 GPs out of 35 general practices can be assumed. Results of a power analysis reveal a medium effect of the intervention with 50 GPs participating in OPAL. A sample size of 50 GPs has approx. 80% power to prove an average pre-post difference of four points in the GP-EoLC-I with assumption of 10 points standard deviation (paired t-test, two-sided 5% significance level) [31].The second target group is formed by relatives of deceased patients. Each independent *n* = 25 relatives are interviewed before and after the intervention phase (work package 3a and 3b).For work package 1a and 1b, *n* = 15 experts/health care stakeholders at the interfaces of PC and GP care (see above) are supposed to be interviewed twice, in both pre and post intervention phase, as a third target group.The fourth target group consists of deceased patients from the participating general practices (work package 4a and 4b). The collection of clinical data is scheduled for six months before and six months after the intervention phase. Gágyor et al. determined an average of 15 cases of death in each general practice per year (standard deviation 7.3, range 4.36) [36]. Consequently, a total of 500 cases of death in twelve months and respectively 250 cases of death in six months in 35 general practices are expected. Thereof about 80% had chronic progressive diseases, so that data from *n* = 200 patients would be available for the analyses in each observation period.With a total of 2.8 million members, the AOK in Lower Saxony represents one-third of all statutory health insured people in Lower Saxony [37]. The health region Hameln-Pyrmont counts about 35.000 members. There are 35.000 cases of death of insured members in one year while the targeted health region sums about 700 cases of death within the insured members of the AOK in Lower Saxony [37].

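### The pre-post tests on deceased patients' data (WP4) assume independent records, although both samples come from the same 35 practices

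*Protocol article*

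**What the plan says.** The Data analysis section assigns a paired t-test to the GP-EoLC-I. For patient parameters in the two phases, "different tests for independent samples will be performed depending of the underlying distribution of the outcome parameters", with the Mann-Whitney U, chi-square and unpaired t-tests as examples. No practice term or covariate is named.

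Phase I describes work package 4a as "Analysis of clinical data of patients with chronic progressive diseases of the 35 collaborating general practices who died within a defined period of time". Phase III says of the follow-up packages, "These work packages will be performed in an equivalent way as described for the work packages 1a-5a". The same 35 practices therefore supply both samples, with different patients in each. Sample size calculation expects that data from "200 patients would be available for the analyses in each observation period", collected over six months on either side of the intervention. The footnotes to Table 1 put this at roughly 4 per project practice.

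Under Ethics and data protection, "Patient data collected and stated by the GPs in the questionnaires will be given anonymously to the research team", and the list linking patients to their IDs stays in the practice. Practice identifiers on the forms are not mentioned.

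**The concern.** Patients of one practice share doctors and referral habits. Several work package 4 indicators, such as outpatient palliative care billing and specialised palliative care prescriptions, are partly decided by the practice, and the intervention acts there too. Two features of the data then matter. Patients are clustered within practice and period, which inflates the variance of the pre-post difference. The same practices appear in both periods, which reduces it. The named tests can represent neither.

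The two periods also contain different people, and work package 4 has no comparison region. The contrast between Lower Saxony and Hameln-Pyrmont belongs to work package 5 and is descriptive. An unadjusted test would attribute any change in the mix of patients, or in the season, to the intervention. At stake are the confidence intervals and p-values of a named secondary outcome, and how its result may be read.

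**Working it through.** **Inputs from the protocol.** 35 practices; 200 deceased patients per period; an "average of 15 cases of death in each general practice per year (standard deviation 7.3, range 4.36"); "a total of 500 cases of death in twelve months and respectively 250 cases of death in six months"; 80% with chronic progressive disease.

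**The plan's own figure.** 500/2 × 0.80 = 200, as stated. Unrounded, 15 × 35 = 525 deaths per year gives 525/2 × 0.80 = 210, so 500 is a mild rounding down.

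**Cluster size.** m = 200/35 = 5.71 per practice and period. The figure of about 4 in Table 1 equals 200/50, which is per GP; 35 practices with 4 each would give only 140. The two statements need reconciling.

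**Assumptions (not in the documents).** ICC 0.05 to 0.10; correlation of practice effects between periods (CAC) 0.3 to 1.0.

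**Formula.** True variance of the pre-post difference relative to the variance assumed by an independent-sample test:

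R = 1 + (m − 1) × ICC − m × ICC × CAC

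Actual two-sided size = 2 × [1 − Φ(1.96/√R)].

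**Results at m = 5.71.**

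| ICC | CAC | R | Actual size |
|---|---|---|---|
| 0.05 | 1.0 | 0.95 | 4.4% |
| 0.05 | 0.5 | 1.09 | 6.1% |
| 0.10 | 1.0 | 0.90 | 3.9% |
| 0.10 | 0.8 | 1.01 | 5.2% |
| 0.10 | 0.5 | 1.19 | 7.2% |
| 0.10 | 0.3 | 1.30 | 8.6% |

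R equals 1 when CAC = (m − 1)/m = 0.825. Above that the test is conservative; below it, too liberal.

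**Unequal practice sizes.** The coefficient of variation is 7.3/15 = 0.487, so the effective m is 5.71 × (1 + 0.487²) = 7.07. At ICC 0.10 and CAC 0.3, R = 1 + 0.607 − 0.212 = 1.39 and the size is 9.7%. A simulation of the unpaired test (8,000 runs per setting), in which practice counts also varied between periods, gave 4.7%, 6.5% and 8.8% at ICC 0.10 and CAC 1.0, 0.8 and 0.5. The formula gives 8.0% at CAC 0.5, so the 9.7% may be a point or so low.

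**With 4 per practice instead.** At ICC 0.10 and CAC 0.3, R = 1 + 0.30 − 0.12 = 1.18 and the size is 7.1%.

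**Case-mix (illustration only).** With 200 against 200 and an outcome near 50%, the standard error is √(2 × 0.25/200) = 5 points. If a patient group whose outcome rate differs by 20 points changes its share by 10 points, the spurious difference is 0.20 × 0.10 = 2.0 points and the rejection rate is 6.9%. A 30-point gap with a 15-point shift gives 4.5 points and 14.7%.

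**Season.** If the six-month windows adjoin a 12-month intervention, the second starts 18 months after the first, so they cover opposite halves of the calendar year. The phase lengths add up to the project (9 + 12 + 15 = 36 months from July 2018). Run consecutively, they would set October to March against April to September.

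**The case against.** The strongest reply is that little depends on this. Work package 4 is secondary, carries no power claim, and sits in a study that places itself at MRC Phase I. The ICC and CAC are assumed, the range of R includes 1, and with 4 patients per practice the upper end is lower. The tests are listed as examples in a condensed article, and covariate adjustment is often left to an analysis plan. Work package 5 also examines the same indicators against the whole of Lower Saxony.

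Much of this stands, and it limits the size of the point. It does not remove it. The examples are open, but the class of test is fixed as independent-sample, and that class does not fit data from the same practices in both periods. The work package 5 comparison is descriptive and not restricted to participating practices, so it does not correct the work package 4 tests.

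A reader might infer that the two samples do differ in case-mix. The documents report no case-mix for either period and apply the same eligibility rule and sudden-death exclusion to both, so this is a risk and not a finding. A reader might also infer that the standard errors must be too small, or that the forms carry no practice code. The first depends on the CAC; on the second the text is silent.

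**Conclusion.** The point holds in limited form. The stated tests do not match the structure of the work package 4 data, and their standard errors are right only if the ICC is zero or clustering and the repetition of practices happen to cancel (CAC near 0.83). Under the assumed ranges, the true size of a 5% test is about 4% to 9%, and about 10% at the unfavourable corner with unequal practice sizes. That is modest, its direction is unknown, and it does not show that any particular work package 4 result would be invalid. Confounding by case-mix or season is a separate risk: the first is not shown to be present, and the second depends on the windows adjoining the intervention. The primary analysis of the GP-EoLC-I is outside this point.

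**What to change.** - **Practice code.** Record a practice code, not a patient identifier, on each anonymised work package 4 questionnaire, or confirm that one is there. This must happen at data collection, because anonymous records may not be traceable to a practice later.
- **Model.** Replace the independent-sample tests with a GEE or mixed model suited to each indicator's type (binary, count or duration), with period as fixed effect and practice as cluster. Add a practice-by-period term only where it can be estimated; with about 4 to 6 patients per practice and period, that will not be so for every indicator.
- **Covariates.** Prespecify age, sex and cancer/non-cancer diagnosis. Omit the last for the chemotherapy indicator, which is defined in cancer patients only.
- **Reporting.** Give the period effect with a 95% confidence interval and call it a pre-post association. Adjustment does not remove secular trend.
- **Text.** Reconcile roughly 4 per practice with 200 from 35 practices, and state the calendar dates of both windows.

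The cost is one extra field on a form and somewhat more complex models. Rare events, such as gastrostomy tube insertion or a first prescription in the last three days of life, will need a simpler cluster-robust method.

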## Discussion

### Provision of PC using SPICT-DE

International research indicates that SPICT™ can increase the awareness of professional health care providers for PC situations and support the systematic initiation of PC actions in both patients with chronic oncological and non-oncological progressive diseases who might benefit from PC [14–16].

The systematic development, refinement and testing of SPICT-DE formed a process of overall five years and was successfully completed by using a multiprofessional and participatory approach [23]. In particular, involving members of the target group of potential users in the development and testing process was important to increase acceptance of SPICT-DE before its implementation. Preliminary research showed that SPICT-DE is a helpful and practical tool to support the identification of patients who might benefit from PC [24].

### Innovative potential and benefit

OPAL is the first study to implement the SPICT-DE regionwide in general practices in Germany. The application, acceptance and efficacy of SPICT-DE as a practical, patient-oriented identification and decision-making tool for patients with chronic progressive diseases who might benefit from PC will be evaluated in mutual experience exchange between GPs and their practice teams, relatives and health care providers and services.

OPAL focusses its intervention at two different levels: (1) general practices and (2) health care providers and services in Hameln-Pyrmont, Lower Saxony. Thus, interprofessional and intersectoral cooperation, communication and coordination of PC for patients at the end of life will be enhanced and optimised.

The introduction of SPICT-DE in the general practice setting in Germany might change the usual identification strategy and possibly increase GP’s awareness in providing PC for patients with different chronic progressive diseases. The tool may contribute to consolidating skills and competencies of GPs in identifying patients with potential PC needs and increase their confidence in initiating PC. The results may also contribute to the overall improvement of care for patients and family caregivers as well as to the optimisation of primary PC by GPs and other health care providers in Germany. Furthermore, the dissemination of the SPICT-DE across the regions may lead to its integration in national strategies to promote PC in the community.

### Expected results

OPAL may contribute to an overall optimisation of care for patients with chronic progressive diseases in the last phase of their lives. GPs play a key role in the systematic identification of patients who might benefit from PC in the primary care setting [3]. The implementation of SPICT-DE allows for a systematic and potentially timely identification of these patients and for initiating specific PC actions which may positively affect the further care of patients and their relatives, e.g. enhancing patient autonomy, participatory decision-making, preventing futile treatment at the end of life [20].

Furthermore, considering the desires, needs and requirements of relatives may identify and avoid overburdening (e.g. due to domestic care or psychosocial burden) preventatively. Thereby, OPAL contributes to a patient-centered and family-oriented care.

At the same time, equitable access to PC may be optimised: so far, especially patients with oncological diseases benefit from PC concepts [40]. The provision of PC is also dependent on the social and educational level. In this study we focus on the needs and desires of patients and their relatives regardless of diagnosis or social background.

The intervention in OPAL may also contribute to an efficient use of resources. European health economic studies indicated that a systematic and structured provision of PC might achieve cost savings for the overall healthcare system [41].

A potential cost saving effect may be due to avoiding therapeutic treatment and unnecessary hospital admission [1, 42, 43]. We expect that the implementation of SPICT-DE may reduce or at least not increase supply costs in the last phase of life whilst improving the quality of care.

### Challenges

Empirically, a selection bias must be taken into account for research projects in general practices. It is much likely, that especially the scientifically interested GPs of the well-established teaching and research practices will be willing to participate. In OPAL, all GPs of the health region will be invited for participation using existing infrastructure of both districts and benefit from well-established information events, coordination centers, working groups and steering committees. The project will be embedded in these existing infrastructures.

For the after-death-interviews relatives of deceased patients of the general practices will be asked for participation. Due to data privacy protection the recruitment and initial invitation will be performed by the GPs and their practice teams and not by the study team. Relatives’ expense and burden will be decreased to a minimum. Relatives will set the time and place of the interviews which will be performed without time pressure and will be stopped at any time upon their request. Experience of prior studies showed that a trustful relationship between the study team and GPs as well as between GPs and the relatives is crucial to promote the recruitment strategy [44, 45]. Nonetheless, a selection bias cannot be fully excluded.

